#### Secondary analyses

The number of blood glucose testing days, glucose readings within acceptable range, medication-adherent days, and physically active days at month 6 will be linearly regressed on binary variables indicating the intervention arms and on the same baseline characteristics as for the primary analysis. If the interventions show statistically significant improvements in HbA1c levels, we will conduct a cost-effectiveness analysis for both intervention arms. The perspective of the cost-effectiveness analysis will be that of the health system. Effectiveness will be measured by the primary outcome and costs will include the average financial incentives paid, labour costs associated to the administration of the incentives, and the cost of devices. The incremental cost-effectiveness ratio between each intervention and UC will be calculated and compared to those of other interventions aiming at reducing HbA1c levels.

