The first primary objective of this trial is to determine whether adding financial incentives to usual care (UC) can improve HbA1c levels among people with suboptimally controlled type-2 diabetes in the primary-care setting. The second primary objective is to determine whether financial incentives should be directed at processes (adherence to blood glucose testing, medication, and daily physical activity) or at achieving intermediary health outcomes (self-monitored blood glucose within acceptable range). This trial will provide novel head-to-head evidence on which strategy works best. In addition, the trial will assess the effect of financial incentives on treatment adherence and whether such incentives constitute cost-effective intervention strategies for diabetes management. Finally, explanatory analysis will aim at determining whether patient perception about diabetes management is altered by the interventions, uncovering factors that might moderate the effect of financial incentives, and identifying socioeconomic groups that may benefit more from the interventions.

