### Objectives

#### Primary objective 1

To determine whether complementing UC with financial incentives for good treatment adherence is superior to UC alone in reducing HbA1c at 6 months.

#### Primary objective 2

To determine whether incentivising intermediate health outcomes (self-monitored blood glucose levels within acceptable range) is superior to incentivising intermediate processes (blood glucose testing, physical activity, and medication adherence) in reducing HbA1c at 6 months.

#### Secondary objective 1

To assess whether complementing UC with financial incentives for good treatment adherence is superior to UC alone in improving treatment adherence as measured by the proportion of glucose tests and medications taken as prescribed and average number of daily steps taken between baseline and 6 months.

#### Secondary objective 2

To assess whether incentivising health outcomes is superior to incentivising intermediate processes in improving treatment adherence as measured by the proportion of glucose tests and medications taken as prescribed and average number of daily steps between taken baseline and 6 months.

#### Secondary objective 3

To assess which intervention (i.e. incentivising health outcomes or processes) has the most favourable incremental cost-effectiveness ratio (ICER) for HbA1c reductions between baseline and 6 months compared to UC alone.

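### Secondary objective 3 compares the two incentive schemes by their separate ICERs against usual care, which can name the wrong scheme when only one would be adopted

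*Protocol article*

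**What the plan says.** Secondary objective 3 (protocol article, Objectives) asks which of the two schemes "has the most favourable incremental cost-effectiveness ratio (ICER) for HbA1c reductions between baseline and 6 months compared to UC alone". The Secondary analyses section plans the matching calculation: "The incremental cost-effectiveness ratio between each intervention and UC will be calculated", and these ratios are then "compared to those of other interventions aiming at reducing HbA1c levels". Its ingredients are stated. On the cost side, the section says that "costs will include the average financial incentives paid, labour costs associated to the administration of the incentives, and the cost of devices". The effect is the change in HbA1c at month 6, since the section also says: "Effectiveness will be measured by the primary outcome".

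The analysis is conditional: "If the interventions show statistically significant improvements in HbA1c levels, we will conduct a cost-effectiveness analysis for both intervention arms".

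The Rationale presents the schemes as alternatives. It asks "whether financial incentives should be directed at processes" or at intermediary health outcomes, and says "This trial will provide novel head-to-head evidence on which strategy works best".

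The article gives no process-versus-outcome ratio, no net-benefit comparison and no value for a percentage point of HbA1c.

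**The concern.** UC, process incentives and outcome incentives are three options of which a health system would adopt one. A ratio against UC shows what each scheme costs per unit of HbA1c reduction when UC is the alternative. It does not show whether the extra effect of the stronger scheme is worth its extra cost over the weaker one, and that is what decides between them. Ranking by separate ratios takes no account of the size of the benefit or of what the payer would give for it. A cheap scheme with a smaller effect can therefore come out as the more favourable one even for a payer who would gladly pay for the larger effect.

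At stake is the answer to secondary objective 3. The criterion is written into the objective and repeated in the analysis, so an analysis plan that follows the article faithfully would carry it forward.

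**Working it through.** The article reports no ICER, so there is no figure of its own to reproduce. The check is of the criterion.

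**The rule in general.** Let C and E be a scheme's extra cost and extra HbA1c reduction over UC, and λ the payer's value of one percentage point.

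- Net benefit over UC = λE − C.
- Suppose B is the more effective scheme (E_B > E_A) and has the higher ratio (C_B/E_B > C_A/E_A). Then B also costs more.
- B is preferred to A when λE_B − C_B > λE_A − C_A, that is, when λ > (C_B − C_A)/(E_B − E_A).
- The stated criterion names A at every λ, so it is wrong for every λ above that between-scheme ratio.
- If the scheme with the lower ratio is also at least as effective, the criterion and net benefit agree at every λ that makes that scheme worth adopting.

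**Inputs for an illustration.**

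- Planning SD of 2, arms of 90 and 60, and a test level of 2.5%: Sample size section.
- Maximum contingent payment per participant: (3.50 + 7 × 0.50 + 7 × 1.00) × 24 = SGD336 in the process arm and 14 × 24 = SGD336 in the outcome arm, both agreeing with the sections on Arms 2 and 3.
- Costs and effects: assumed. The costs are below SGD336. The effects are chosen large enough to meet the significance condition.

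| | Extra cost over UC | Extra effect over UC | ICER against UC |
|---|---|---|---|
| Scheme A | SGD120 | 0.9 points | 120/0.9 = SGD133 per point |
| Scheme B | SGD240 | 1.2 points | 240/1.2 = SGD200 per point |

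B against A: (240 − 120)/(1.2 − 0.9) = 120/0.3 = SGD400 per point.

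| λ (SGD per point) | Net benefit of A | Net benefit of B | Preferred |
|---|---|---|---|
| 300 | 270 − 120 = 150 | 360 − 240 = 120 | A |
| 400 | 360 − 120 = 240 | 480 − 240 = 240 | equal |
| 500 | 450 − 120 = 330 | 600 − 240 = 360 | B |

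The stated criterion names A in all three rows.

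**Would the analysis be run on these figures?** For one scheme against UC, SE = 2 × √(1/90 + 1/60) = 0.333.

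- 0.9/0.333 gives z = 2.7 and 1.2/0.333 gives z = 3.6. Both exceed 2.24, the two-sided critical value at 2.5%.
- With 76 and 51 participants, the numbers required before the attrition allowance, SE = 2 × √(1/76 + 1/51) = 0.362. Then z = 2.5 and 3.3, still above 2.24.
- Effects of 0.3 and 0.6 points would give z = 0.9 and 1.8 with full arms. At SD 2 they would not trigger the analysis, so they cannot serve as an illustration.

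**The case against.** Five points can be made for the plan.

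1. **Ratios against UC have a proper use.** The Rationale and the Discussion also ask whether incentives are cost-effective at all, and the Secondary analyses section sets the ratios beside those of other HbA1c-lowering interventions. This stands. A reader might infer that process versus outcome is the trial's whole economic question, but the article does not say so. Even so, secondary objective 3 does ask which of the two schemes is the more favourable, and it answers by the ratios against UC.

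2. **No adoption decision is written down.** The objective is to assess, and no threshold or recommendation follows. That is fair, and it limits the consequence. But a ranking of two alternatives will be read as guidance on which to choose.

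3. **The missing ratio can be derived later.** Both arms' effects are estimated against the same UC reference, and incentive cost and administration time are recorded in both incentive arms. This stands and makes the repair cheap. The stated criterion would still name a scheme on the wrong ratio.

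4. **The failure is conditional.** It needs the particular pattern shown in the working, and significant HbA1c effects first. A reader might infer that the plan will pick the wrong scheme. The article does not support that, because it gives no costs, effects or threshold that would place the trial in that region. The illustrative effects are also large: 1.2 points exceeds the 1-point difference used for the sample size. The 0.3-point gap between schemes would itself be imprecise, with z = 0.3/(2 × √(2/90)) = 1.0.

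5. **An article condenses a fuller plan.** Bootstrap intervals and acceptability curves may properly be left to that plan, and their absence is not part of this point. The criterion itself is stated, so it is not a detail left out.

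**Conclusion.** The concern holds as a fault in a stated criterion. Comparing the schemes by their separate ICERs against UC misidentifies the preferred one when two things are both true: the more effective scheme has the higher ICER against UC, and willingness to pay exceeds the ICER between the schemes. On the assumed figures the stated criterion names the scheme at SGD133 per point, while the other is preferred for any value of a point above SGD400.

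The algebra does not depend on the assumed costs and effects, but the SGD400 does. It also rests on the schemes being alternatives, as the Rationale presents them. That the illustration would reach the analysis rests on the planning SD of 2. How likely the trial is to fall in the failure region cannot be judged from the article.

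The consequence is limited to a secondary economic analysis that is conditional on significant HbA1c effects. The primary inference is not affected. The change is still worth making, because as written secondary objective 3 can return the wrong scheme.

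**What to change.** Reword secondary objective 3 and the matching sentence in the Secondary analyses section so that the choice between schemes rests on a full incremental comparison of the three arms:

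- order UC, process and outcome by mean cost;
- drop any option that is dominated or extendedly dominated;
- report the ICER of each remaining arm against the next less costly one, including process versus outcome where both remain.

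Keep the ratios against UC, labelled as serving the comparison with other HbA1c-lowering interventions. Showing the joint uncertainty of costs and effects, for example by bootstrap, is optional.

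The cost is a change of wording in two places and a little more analysis on data already planned for collection. It is best settled before the final costs and effects by arm are examined.

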### Explanatory analyses

The same model as for the primary analysis will be conducted with changes from baseline in HbA1c levels at months 12 and 18. Logistic regressions of binary variables indicating whether the participants have had a titration change of their oral medicine, and whether they have switched to insulin therapy at months 6, 12 and 18 will be estimated. Linear regressions of the changes from baseline in EQ-5D-5L, BIPQ, SMBG, BMQ and DSCA scores at month 6 will also be estimated. For all models, the covariates will be binary variables indicating the intervention arms and the same other baseline characteristics as for the primary analysis. Next, the models used in the primary and secondary analyses will be extended by adding interaction terms between potential intervention moderators (gender, age, language spoken, education, occupation, income, EQ-5D-5L, BIPQ, SMBG, BMQ and DSCA scores, and binary variables indicating comorbidities) and the binary variables indicating study arms. In particular, this analysis will be used to determine the benefit incidence of the intervention according to socioeconomic factors.

### Ethics and dissemination

This study has been approved by the SingHealth Centralised Institutional Review Board E (Ref 2013/830/E) which oversees family medicine research at SingHealth. The principal investigator is responsible for informing the CIRB of any amendments to the protocol or other study-related documents, as per local requirements.

The consent process will be carried out at the SingHealth Polyclinic in Geylang. Interested and potentially eligible patients will be referred for the study by a physician at the polyclinic. Alternatively, patients may respond to study posters or newspaper advertisements and contact the CRC directly. In all cases the CRC will explain the study to the patient in either English or Mandarin. The Participant Information Sheet and Consent Form (see Additional files 8 and 9), and all other participant documents will be available in both English and Mandarin. Patients are expected to be able to give consent to participate in the study on their own. No arrangements have been made for informed consent to be taken from a legally acceptable representative of the patient. No provisions have been made to compensate participants for research-related injuries as the study does not involve more than minimal risks. However, compensation may be considered on a case-by-case basis for unexpected injuries due to non-negligent causes.

A unique participant ID will be assigned to all patients who are successfully enrolled on the study. Study questionnaires and checklists will only refer to the participants using this ID number. In addition, data is de-identified before is it passed to Duke-NUS. Records containing identifiable data, such as the screener and Consent Form, will be stored in locked cabinets at the polyclinic with restricted access. All study materials, such as study devices, will be kept in locked cabinets at the polyclinic and Duke-NUS. Only the investigators and authorised personnel directly involved with the study will have access to the data. All data files will be password protected and stored on a secure server at Duke-NUS for 10 years and then securely destroyed.

Investigators will have unrestricted access to the research data upon completion of the trial. Main trial results will be published irrespective of the magnitude and direction of the effects and their statistical significance. To be listed as authors, investigators will have to meet all four conditions for authorship recommended by the International Committee of Medical Journal Editors (ICMJE) [33]. Those investigators and collaborators who do not meet all four criteria will be acknowledged for their contribution.

## Discussion

The primary objectives of this randomised controlled trial are to determine whether adding financial incentives to UC can improve HbA1c levels among people with suboptimally controlled diabetes in a primary-care setting; and to determine whether financial incentives should be directed at processes or at achieving intermediary health outcomes. In order to meet these objectives it will be crucial that participants fully understand the goals and rewards of their study arm. First, participants must not confuse the non-contingent incentives received to compensate for their time taking part in the trial with the process and outcome incentives that participants in the intervention arms can receive if they meet their goals. Second, it is important to make sure that participants understand the calculation of the incentive amount that they can expect to receive based on their diabetes self-management efforts. Great care will be taken by the CRC to explain the incentive scheme during the baseline visit. In addition, the CRC will check whether the participants remember the incentive calculation at the month-3 and month-6 visits, will re-explain the calculations if necessary, and will record whether the calculations were understood in order to assess the quality of the study. The Participant Leaflets also contain a detailed section on incentive goals and calculation for the study arm the participants have been randomly assigned to.

The possibility of gaming has also been considered. In order to earn incentives without improving their diabetes management, some participants might, for instance, ask a third person to use their device, shake their pedometer to gain extra steps, and open and close their tracking device without taking their medication. In efforts to contain gaming, participants will be asked to sign a participation oath which has been shown to decrease the likelihood of cheating in other studies [34] and has been applied to financial incentives studies [15, 35]. Furthermore, several quality checks will be performed. Participants will be asked to keep all their medication bills and bring them to the clinic visits. In order to assess the validity of pedometer data, the distribution of steps within days will be examined to detect implausible patterns. Glucometer readings data will be compared to HbA1c levels in efforts to detect implausible discrepancies. It is worth noting that, if present, gaming would not affect the primary analysis as it is based on HbA1c tests.

We will first compare our primary results to the only other incentive study that reports HbA1c levels as a primary outcome [18]. We will then compare our results to those found in other types of diabetes management interventions such as education [7], blood glucose self-monitoring alone [8], free-living physical activity [9], computer-based interventions [10] and quality improvement strategies [11]. This study will provide evidence on whether financial incentives can cost-effectively improve diabetes management. It will also be important to determine who benefits the most from the intervention. By interacting socioeconomic characteristics with the intervention effect, this study will provide evidence on the benefit incidence of interventions involving financial incentives. Last, by comparing process to outcome incentives, this study will inform the design of future incentive strategies in chronic disease management and beyond.

## Trial status

Recruitment to the TRIAD study began in February 2015 and is ongoing. As of 31 May 2017, 140 participants (58.3% of the total sample size) have been enrolled in the study.

## Abbreviations

BIPQ: Brief Illness Perception Questionnaire
BMQ: Beliefs about Medication Questionnaire
CIRB: Centralised Institutional Review Board
DSCA: Diabetes Self-Care Activities
EQ-5D-5L: European Quality of Life-5 Dimensions-5 Levels
HbA1c: Glycated haemoglobin
PARQ: Physical Activity Readiness Questionnaire
SAE: Serious Adverse Events
SGD: Singapore dollar
SMBG: Self-Monitoring of Blood Glucose
TRIAD: Trial to Incentivise Adherence for Diabetes
UC: Usual care
